|--|----------------------------------------------------------------------------------------------------------------------------------------------------------------------------------------------------------------------------------------------------------------------------------------------------------------------------------------------------------------------------------------------------------------------------------------------------------------------------------------------------------------------------------------------------------------------------------------------------------------------------------------------------------------------------------------------------------------------------------------------------------------------------------------------------------------------------------------------------------------------------------------------------------------------------------------------------------------------------------------------------------------------------------------------------------------------------------------------------------------------------------------------------------------------------------------------------------------------------------------------------------------------------------------------------------------------------------------------------------------------------------------------------------------------------------------------------------------------------------------------------------------------------------------------------------------------------------------------------------------------------------------------------------------------------------------------------------------|
|  | 
committee (consisting of experts in hematology, infection, pathology, pharmacy, and statistics) judge whether adverse events are treatment-related or non-treatment-related. Serious adverse events are those that resulted in death, disability, or incapacity, are life-threatening or judged an important medical event, or required hospitalization or prolongation of existing hospitalization.
 
 
● The descriptive analysis of patient characteristics included median and interquartile range (IQR) for continuous variables, and absolute and relative frequencies for categorical variables. The time-to-event endpoints including OS, EFS and DFS were analyzed by the Kaplan-Meier method and compared using the log-rank tests. The corresponding hazard ratio (HR) and 95% CI were estimated using the Cox proportional hazards model. The cumulative incidences of relapse were calculated by accounting for competing risks, and non-relapse mortality was a competing risk for relapse. The comparison of the cumulative incidence in the presence of a competing risk was done using the Fine and Gray model. All variables in the Cox models were tested for proportional hazards assumption. Factors that were significant at the 0.1 level from the univariable model were included in the multivariable model. All statistics were analyzed in software R version 4.1.0 (R Development Core Team, Vienna, Austria) or Stata version 15.1 (StataCorp [name]) or SPSS version 22.0 (SPSS, Chicago, IL). All statistical tests were two-tailed with a significance level of 0.05.
 
 |
|--|----------------------------------------------------------------------------------------------------------------------------------------------------------------------------------------------------------------------------------------------------------------------------------------------------------------------------------------------------------------------------------------------------------------------------------------------------------------------------------------------------------------------------------------------------------------------------------------------------------------------------------------------------------------------------------------------------------------------------------------------------------------------------------------------------------------------------------------------------------------------------------------------------------------------------------------------------------------------------------------------------------------------------------------------------------------------------------------------------------------------------------------------------------------------------------------------------------------------------------------------------------------------------------------------------------------------------------------------------------------------------------------------------------------------------------------------------------------------------------------------------------------------------------------------------------------------------------------------------------------------------------------------------------------------------------------------------------------|

## Abbreviations

|           |                                                         |
|-----------|---------------------------------------------------------|
| R/R       | Relapsed/refractory                                     |
| AML       | Acute myeloid leukemia                                  |
| CR        | Complete remission                                      |
| CRi       | Complete remission with incomplete hematologic recovery |
| PR        | Partial remission                                       |
| NR        | Non-remission                                           |
| ORR       | Overall response rate                                   |
| CRc       | Composite complete remission                            |
| OS        | Overall survival                                        |
| DFS       | Disease-free survival                                   |
| VEN       | Venetoclax                                              |
| AZA       | Azacitidine                                             |
| HHT       | Homoharringtonine                                       |
| VAH       | VEN+AZA+HHT                                             |
| DLI       | Donor lymphocyte infusion                               |
| Allo-HSCT | Allogeneic haematopoietic stem-cell transplantation     |
| MRD       | Minimal residual disease                                |
| ECOG      | Eastern Cooperative Oncology Group                      |
| ULN       | Upper limit of normal                                   |
| ALT       | Alanine aminotransferase                                |
| AST       | Aspartate aminotransferase                              |
| GVHD      | Graft-versus-host disease                               |
| HMA       | Hypomethylating agents                                  |
| ITT       | Intent-to-treat                                         |
| IQR       | Interquartile range                                     |
| HR        | Hazard ratio                                            |
| CI        | Confidence interval                                     |

|       |                                                |
|-------|------------------------------------------------|
| BCL-2 | Anti-apoptotic B-cell lymphoma 2               |
| MCL1  | Myeloid-cell leukemia 1                        |
| BM    | Bone marrow                                    |
| PB    | Peripheral blood                               |
| CRF   | Case report form                               |
| SAEs  | Serious adverse events                         |
| AEs   | Adverse events                                 |
| CTCAE | Common Terminology Criteria for Adverse Events |
| GCP   | Good clinical practice                         |

## 1. Introduction

---

Acute myeloid leukemia (AML) is one of the major diseases threatening human health. Refractory and relapse (R/R) are the most important reason for the failure of AML treatment, which eventually lead to the progression of more than one half of AML patients. At present, the low remission rate, short time of survival and lack of well-accepted and effective treatment are the main problem of R/R AML. The exact mechanism of drug resistance in R/R AML is not yet up until now completely clear. Clinical trials are the first choice for the treatment of R/R AML which is recommended in the National Comprehensive Cancer Network (NCCN) guideline to improve the efficacy of this group of patients. Therefore, the current difficulty and focus of the research in R/R AML is to further clarify the mechanism of drug resistance and explore a safe and effective therapy.

The high expression of anti-apoptotic B-cell lymphoma 2 (BCL-2) is an important reason for drug resistance in AML . Combination of BCL-2 inhibitor venetoclax (VEN) with hypomethylating agents (HMAs) or low dose cytarabine have achieved good results in the elderly or unfit-AML patients, and approved by FDA and recommended by NCCN guidelines for the recommended treatment of elderly and unfit-AML . Also, R/R AML patients have achieved encouraging results with the salvage treatment of VEN-based therapy, but the CR rate is not as high as expected, and the duration of complete remission is short . Furthermore, the curative effect in the patients relapsed after allo-HSCT is very poor. Therefore, how to improve the efficacy of VEN-based regimen and overcome VEN resistance are an urgent problem to be solved.

High expression of myeloid-cell leukemia 1 (MCL1) and BCL-XL is recognized as an important factor for VEN resistance . Studies  have revealed that inhibition of MCL-1 expression can improve the anti-leukemia effect of VEN. Homoharringtonine (HHT), widely used in the treatment of hematological malignant tumors in China since the 1970s. HHT has also received more widespread attention and approved by the FDA in 2010 for the treatment of R/R CML  and AML , is

reported to inhibit the expression of MCL-1 and BCL-XL in leukemic cells. The previous study  had reported that HHT combined with VEN could further inhibit the expression of MCL-1 and BCL-2 in lymphoma cells and increase the anti-lymphoma effect, suggesting that HHT might enhance the anti-tumor effect of VEN. Our preliminary study showed that HHT enhanced the anti-leukemia effect of VEN with or without AZA through deeper inhibition of MCL1, BCL-XL in AML cell lines. To further optimise salvage therapy for R/R AML patients, we set up a multicenter, phase 2 trial to investigate the efficacy and tolerability of VAH regimen in patients with R/R AML.

## **2. Study objectives**

### **2.1 Primary Objective**

The primary endpoint is CRc rate after 2 cycles of trial treatment.

### **2.2 Secondary Objectives**

The secondary endpoints are safety, overall survival (OS), event-free survival (EFS), disease-free survival (DFS), and relapse. OS is defined as the time from treatment until death or censored at the last follow-up. EFS is defined as the time from treatment until documented failure to achieve CRc, relapse after CRc, or death from any cause, whichever occurred first. DFS is defined as the time from the date of CRc until relapse, death from any cause, or censored at the last follow-up.. Data for each patient are censored at the date of the last visit or the date on which the patient is last known to be alive.

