| determination        | 
assumption that the VAH regimen would achieve a higher CRc rate compared with historical CRc rate of 45% (on the basis of the venetoclax in combination with HMAs study in R/R AML). To identify a 15% absolute improvement in CRc with VAH regimen, a total of 87 patients was required to provide the study with a significance level of 5% and a power of 80%. After adjusting for a 10% dropout, the total planned sample size was 96 patients. The sample size calculation was done using PASS software, version 11.0.
                                                                                                                                                                                                                                                                                                                                                                                                                                                                                                                                                                                                                                                                                          |
| Statistical analysis | 
Statistical analysis is performed based on the intent-to-treat (ITT) population, which includes all subjects
 
 
● The primary endpoint is CRc rate after 2 cycles of trial treatment.
 
● The secondary endpoints are safety, overall survival (OS), event-free survival (EFS), disease-free survival (DFS) and relapse.
 
 
OS is defined as the time from treatment until death or censored at the last follow-up.
 
EFS is defined as the time from treatment until documented failure to achieve CRc, relapse after CRc, or death from any cause, whichever occurred first.
 
DFS is defined as the time from the date of CRc until relapse, death from any cause, or censored at the last follow-up.
 
Data for each patient are censored at the date of the last visit or the date on which the patient was last known to be alive.
 
 
● Adverse events are recorded up to 4 weeks after the discontinuation of the trial therapy, and are graded according to the National Cancer Institute Common Terminology Criteria for Adverse Events (CTCAE) version 4.0. The study adjudication
 
 |

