### **5.3 Follow-up**

The clinical data cutoff date is June 30, 2022. Disease assessment including routine blood and BM assessment will be regularly performed post-salvage therapy. For response assessments, bone marrow is evaluated on cycle 1 day 28 and again 1-2 weeks after hematological recovery if the day 28 bone marrow is aplastic. Subsequent bone marrow evaluations are done before and after cycles 2, and then as clinically needed. Adverse events are recorded up to 4 weeks after the discontinuation of the trial therapy, and are graded according to the National Cancer Institute Common Terminology Criteria for Adverse Events version 4.0.

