## **6. Efficacy Assessments**

### **6.1 Definitions**

- Relapse is defined as reappearance of leukemic blasts in the peripheral blood or  $\geq$  5% blasts in the BM as pirate or biopsy not attributable to any other cause or reappearance or new appearance of extramedullary leukemia after achieving CRc.

CR is defined as BM blasts <5%; absence of circulating blasts and blasts with Auer rods; absence of extramedullary disease; ANC  $\geq 1.0 \times 10^9/\text{L}$  and PLT  $\geq 100 \times 10^9/\text{L}$ .

CRi is defined as all CR criteria except for incomplete hematologic recovery with neutropenia  $< 1.0 \times 10^9/\text{L}$  and/ or thrombocytopenia  $< 100 \times 10^9/\text{L}$ .

PR is defined as a minimal residual disease of 5-25% with a greater than 50% decrease in leukemic blast percentage.

NR is defined as a failure to obtain CRc or PR.

CRc comprises CR and CRi.

ORR includes CRc and PR.

The MRD level of 0.01% is used as a threshold to distinguish MRD positive (MRD+) from MRD negative (MRD).

OS is defined as the time from treatment until death or censored at the last follow-up.

EFS is defined as the time from treatment until documented failure to achieve CRc, relapse after CRc, or death from any cause, whichever occurred first.

DFS is defined as the time from the date of CRc until relapse, death from any cause, or censored at the last follow-up.

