## **9. Rules of Withdrawal**

### **9.1. Subjects Withdraw from the Study**

Subjects can withdraw from the study at any time for any reason without impact on the investigator's right to treat disease for subjects. Based upon the interest of subjects, the investigator has the right to request subjects to withdraw from the study for any

reason including concomitant disease, AEs or treatment failure. The core group of clinical study reserves the right to request subjects to withdraw from the study for deviation(s) from the protocol, administrative reasons, or other effective or ethical reasons.

The last assessment for subjects must be performed and documented in the CRF regardless of the time and reason for withdrawal. The reason for withdrawal from study participation must be documented in the CRF. All documents related to subjects should be completed. Despite withdrawal from the study, those subjects should be followed up and documented about their diseases until withdrawal of informed consents.

For subjects who withdraw from the study due to concomitant diseases or AEs, the details must be documented in the CRF with other appropriate and valuable data attached.

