### **10.3 Contents**

The contents of every follow-up visit include complaints of subjects, vital signs, physical examination, clinical symptoms and clinical laboratory evaluations (hematology, serum chemistry, urinalysis, electrocardiogram, chest imaging examination, and BM assessment). All of the results must be documented in the original medical record.

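### One censoring rule for OS, EFS and DFS lets a bare record of being alive count as relapse-free time

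*Protocol*

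**What the plan says.** Section 2.2 of the Protocol defines OS, EFS and DFS and then closes with one sentence for all patients: data are "censored at the date of the last visit or the date on which the patient is last known to be alive". The Study Synopsis repeats it under the secondary objectives and under statistical analysis.

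- **EFS** has no other censoring rule: "EFS is defined as the time from treatment until documented failure to achieve CRc, relapse after CRc, or death from any cause, whichever occurred first".
- For **DFS**, the definition adds only the last follow-up: "DFS is defined as the time from the date of CRc until relapse, death from any cause, or censored at the last follow-up" (Section 6.1).
- **Relapse** is established from blood, marrow or extramedullary disease (Section 6.1). Its cumulative incidence is estimated with non-relapse mortality as the competing event (Section 11.4.2.2).

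The assessment schedule is stated in two ways. Section 5.3 says: "Subsequent bone marrow evaluations are done before and after cycles 2, and then as clinically needed", and Sections 3 and 6.4 say the same. Section 10.3 lists among the contents of every follow-up visit "clinical laboratory evaluations (hematology, serum chemistry, urinalysis, electrocardiogram, chest imaging examination, and BM assessment", and Section 10.2 sets visits weekly for three months and then monthly. After withdrawal, Section 9.1 says: "Despite withdrawal from the study, those subjects should be followed up and documented about their diseases until withdrawal of informed consents".

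**The concern.** A contact showing that a patient is alive rules out death. It does not rule out relapse. If a responder's last blood or marrow result is from month 4 and the last record of being alive is from month 12, the rule permits DFS to be censored at month 12. The eight months in between enter the risk set as relapse-free although nobody looked.

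Two details add to this. The two dates are joined by an unordered 'or', so the rule does not fix one date per patient. EFS counts failure to reach CRc only when it is documented, so a living patient who leaves without CRc and without a response marrow would be censored. If the ITT analysis of CRc (Section 11.4.1, all enrolled subjects) counts that patient as a non-responder, the two endpoints treat the same patient differently.

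At stake are secondary estimates reported for a single-arm regimen, with an error that can only favour VAH.

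**Working it through.** **No protocol figure to reproduce.** The protocol gives no median, rate or event count for EFS or DFS. The check is therefore on direction, with an illustration of size on assumed inputs.

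**Direction.** Let T be the true time to relapse or death, and T* the time recorded under the rule when relapse after a certain point goes unseen. A missed relapse is replaced by the later death or by censoring, so T* is never earlier than T. With an independent data cutoff, Kaplan-Meier then estimates S*(t) ≥ S(t). The excess at time t is the probability of having relapsed unseen before t and still being alive at t. The same ordering applies to EFS. For cumulative relapse, an unseen relapse is either never counted or counted as death without relapse, so the incidence falls. Only DFS was computed; the statements on EFS and relapse rest on this argument.

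**Size.** Assume exponential times with rates λr (relapse), λn (death without relapse) and λd (death after relapse), each ln 2 divided by its median. A share f of responders stops disease assessment at time s, unrelated to relapse, while vital status is still followed. Then

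excess(12) = f × average over s of ∫ from s to 12 of λr · exp(−(λr+λn)u) · exp(−λd(12−u)) du.

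*Set A.* Median time to relapse 10 months, death without relapse 40, survival after relapse 5; s uniform on 1 to 12 months.
- True 12-month DFS: 2^−(12/10 + 12/40) = 2^−1.5 = 35.4%.
- λr = 0.0693, λd = 0.1386, λr+λn = 0.0866, difference λd − (λr+λn) = 0.0520.
- exp(−12λd) = 0.1895, exp(12 × 0.0520) = 1.866, mean of exp(0.0520 s) over 1 to 12 = 1.421.
- Integral: 0.0693 × 0.1895 × (1.866 − 1.421) / 0.0520 = 0.112.
- Excess: 1.1, 2.2 and 3.4 points for f = 10%, 20% and 30%. Simulation on these inputs, with the data cutoff uniform on 6 to 24 months, agrees: about 36.4%, 37.6% and 38.7%.

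*Set B.* True median DFS 6, 9 or 12 months; 75% of first events are relapses; median survival after relapse 6 months; s uniform on 1 to 6 months; data cutoff uniform on 3 to 24 months. Simulated 12-month DFS and median under the stated rule:

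| True median | True 12-month DFS | f = 10% | f = 20% | f = 30% |
|---|---|---|---|---|
| 6 months | 25% | 26.9%, 6.2 months | 28.8%, 6.5 months | 30.6%, 6.7 months |
| 9 months | 40% | 41.4%, 9.4 months | 43.1%, 9.8 months | 44.4%, 10.2 months |
| 12 months | 50% | 51.3%, 12.4 months | 53.1%, 13.1 months | 54.3%, 13.6 months |

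The overstatement is about 1.5 to 5.5 points, or 0.2 to 1.7 months on the median. As a check on the first row, with true median 6 the integral is 0.75 × (ln 2/6) × 0.25 × (12 − 3.5) = 0.184, which gives 1.8, 3.7 and 5.5 points.

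**At f = 0** the excess is zero in both sets.

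**Censoring at the last disease assessment** returns the true curve in both sets, provided that later deaths are not counted either. If survivors are censored at the last assessment while deaths after the gap still count as events, Set A gives 35.0%, 34.7% and 34.4%, a bias of about −0.3 to −0.9 points. The fix must therefore cover deaths.

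**The case against.** The best defence is that the protocol plans to keep looking for relapse. Sections 5.3 and 6.4 ask for regular blood and marrow assessment after salvage therapy. Sections 10.2 and 10.3 set frequent visits with blood counts and marrow. Relapse can be found in peripheral blood. Section 4.2 requires a final visit covering laboratory tests and disease status. On that plan a last visit is a disease assessment, and censoring there is largely right. This stands, and it confines the problem to the last-known-alive part of the rule.

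Three stronger readings are tempting, and the protocol does not support them:

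- A reader might infer that withdrawn patients are followed for survival only. Section 9.1 asks for follow-up of their disease.
- A reader might infer from the as-needed marrow wording that nobody looks for relapse after cycle 2. Section 10.3 says otherwise. The conflict shows an unsettled schedule, not an absence of assessment.
- A reader might infer that the later date will be picked patient by patient. The unordered wording permits it; nothing says it will be done.

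It is also fair that the size is modest. With 58 responders (about 60% of 96), the sampling standard deviation of 12-month DFS is about 6.7 points on the Set A inputs, so 3.4 points is about half of it. But sampling error has no preferred sign, and this error does. The defence also does not change the written rule, which allows an alive-only date whenever assessment lapses. Since the schedule contradicts itself, it cannot serve as a firm safeguard.

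**Conclusion.** The point holds for the last-known-alive date applied to EFS, DFS and cumulative relapse. The rule is stated in the protocol and fixed badly, so this is not a detail left to an analysis plan. The bias can only raise EFS and DFS and lower relapse. On assumed inputs, 12-month DFS is overstated by about 1 to 3.5 points when 10 to 30% of responders have only vital status followed, by up to about 5.5 points with earlier loss of assessment and faster relapse, and not at all when disease follow-up is complete. The protocol does not give that share, and following Section 9.1 would reduce it. These figures assume exponential times and a stop in assessment unrelated to relapse.

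The primary endpoint (CRc after 2 cycles) and the sample size do not depend on this rule. It should be changed, but it does not threaten the trial's main conclusion.

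**What to change.** 1. Split the sentence in Section 2.2 and in both synopsis entries. Censor OS at the date last known alive. Censor EFS, DFS and relapse at the last disease assessment (blood or marrow) showing no relapse.
2. State how a death after a gap in assessment is handled, define the gap, and run a sensitivity analysis the other way.
3. In EFS, count patients who leave without ever reaching CRc as failures, consistent with the ITT analysis of CRc, at a date stated in advance. The last response assessment, or day 1 if there is none, is one convention among several; what matters is fixing one.
4. Reconcile the as-needed marrow schedule (Sections 3, 5.3 and 6.4) with marrow at every visit (Sections 10.2 and 10.3), so that the last disease assessment has one meaning.
5. Report how many responders have a last-alive date later than their last disease assessment, and by how much.

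The cost is wording and minor programming. EFS and DFS estimates become slightly less favourable if assessment gaps exist, and barely move if they do not.
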